# Pancreatitis, very early compared with normal start of enteral feeding (PYTHON trial): design and rationale of a randomised controlled multicenter trial

**DOI:** 10.1186/1745-6215-12-73

**Published:** 2011-03-10

## Abstract

**Background:**

In predicted severe acute pancreatitis, infections have a negative effect on clinical outcome. A start of enteral nutrition (EN) within 24 hours of onset may reduce the number of infections as compared to the current practice of starting an oral diet and EN if necessary at 3-4 days after admission.

**Methods/Design:**

The PYTHON trial is a randomised controlled, parallel-group, superiority multicenter trial. Patients with predicted severe acute pancreatitis (Imrie-score ≥ 3 or APACHE-II score ≥ 8 or CRP > 150 mg/L) will be randomised to EN within 24 hours or an oral diet and EN if necessary, after 72 hours after hospital admission.

During a 3-year period, 208 patients will be enrolled from 20 hospitals of the Dutch Pancreatitis Study Group. The primary endpoint is a composite of mortality or infections (bacteraemia, infected pancreatic or peripancreatic necrosis, pneumonia) during hospital stay or within 6 months following randomisation. Secondary endpoints include other major morbidity (e.g. new onset organ failure, need for intervention), intolerance of enteral feeding and total costs from a societal perspective.

**Discussion:**

The PYTHON trial is designed to show that a very early (< 24 h) start of EN reduces the combined endpoint of mortality or infections as compared to the current practice of an oral diet and EN if necessary at around 72 hours after admission for predicted severe acute pancreatitis.

**Trial Registration:**

ISRCTN: ISRCTN18170985

## Background

In 20% of patients, acute pancreatitis is complicated with peripancreatic and pancreatic necrosis [1]. In about 30% of these patients, this necrotic tissue becomes infected and this is associated with a mortality rate of approximately 15% [2,3]. In addition to infected necrosis, other infections such as bacteraemia and pneumonia frequently occur with a major negative impact on outcome [4,5]. Attempts to reduce infections with the prophylactic use of antibiotics were unsuccessful [6,7]. The current hypothesis is that these infections originate from the gut. Gut-derived bacteria translocate due to a combination of pathophysiological events - disturbed gastrointestinal motility, bacterial overgrowth, reduction of arterial blood flow, increased permeability of the gastrointestinal mucosal barrier and bacterial translocation - leading to distant systemic infections, including infection of peripancreatic or pancreatic necrosis [8-11]. These phenomena already occur within a few hours after onset of symptoms and cause early infections [12-14]. This implies that there is only a very narrow time-window for reducing bacterial translocation and subsequent infections [5]. In clinical practice, patients with predicted severe acute pancreatitis are generally kept at a 'nil per mouth' regimen until the disease severity becomes clear. After a few days, some patients can start an oral diet while others require a nasojejunal catheter for enteral nutrition. This usually takes 3 to 4 days and the deleterious effects on the gastrointestinal tract already have taken place [1].

Enteral nutrition (EN) has the ability to maintain gut integrity, stimulate gut contractility and the release of immunomodulating agents and blood flow to the gut [15]. The maintenance of blood flow, preserved motility and gut mucosal integrity theoretically reduce bacterial overgrowth and bacterial translocation and thereby potentially reduces the number of infections. Furthermore, maintaining mucosal integrity reduces the release of inflammatory mediators, decreases oxidative stress and abates the systemic inflammatory response syndrome (SIRS) [16]. EN has already proven superior to parenteral nutrition in reducing mortality and infections in predicted severe pancreatitis [17]. In intensive care patients with other diseases, a meta-analysis of randomised trials demonstrated a reduction of infections following a very early start of enteral nutrition [18]. A 2009 systematic review suggested that also in patients with acute pancreatitis a very early start of EN improves outcome [19].

The PYTHON trial was designed to investigate whether a start of EN within 24 hours after admission counteracts the early deleterious effect of SIRS on bowel mucosa and reduces infections and mortality in predicted severe acute pancreatitis, as compared to a start of EN after 72 hours.

## Methods

### Design

The PYTHON trial is a randomised controlled, parallel-group, superiority multicenter trial. Patients will be randomly allocated to receive EN within 24 hours through a nasojejunal catheter or start after 72 hours of admission with an oral diet if tolerated or EN through a nasojejunal catheter if necessary. Patients with a primary episode of predicted severe acute pancreatitis are eligible for randomization.

The aim of the study is to investigate whether the clinical outcome can be improved by a very early start of EN, as compared to the current practice of an oral diet and EN if necessary, i.e. at around 72 hours after admission.

### Primary endpoint

The primary endpoint is a composite of mortality or infections (i.e. bacteraemia, pneumonia and infected necrosis; see Table 1 for definitions) occurring during hospital admission or within 6 months following randomisation. Re-admission within 10 days after initial hospital discharge is considered part of the index admission.

**Table 1 T1:** Primary endpoint: definition of infections

Infection	Definition
Infected pancreatic necrosis	Positive culture of pancreatic or peripancreatic necrotic tissue obtained by means of fine-needle aspiration or from the first drainage procedure or operation, or the presence of gas in the fluid collection on contrast-enhanced CT.

Bacteraemia	Positive blood culture. For non-pathogens (eg. coagulase negative staphylococci) at least 2 samples have to be positive.

Pneumonia	Coughing or dyspnoea, radiography with infiltrative abnormalities, raised inflammatory variables and positive sputum culture. On the intensive care unit a positive endotracheal culture is mandatory.

### Secondary endpoints

Attenuation of the acute inflammatory response is hypothesized to be part of the beneficial effect of very early feeding on outcome thus secondary endpoints to assess such an effect are:

• Daily APACHE-II scores (see Additional file 1; Table S3), SIRS (presence, onset, duration, see Additional file 1; Table S4), CRP, and white cell count during the first week following randomisation.

• The individual components of the primary endpoint, need for and number of interventions (percutaneous or endoscopic transgastric drainage, surgical or endoscopic necrosectomy, other operations), use of antibiotics, length of hospital stay and in-hospital mortality.

• New onset organ failure (single or multi-system organ failure, timing and duration of failure), daily Marshall scores and need for and duration of ICU admission at any time during follow-up (for definitions see Additional File 1; Table S1 and Table S2).

Other secondary outcome measures are:

• The presence of peripancreatic and pancreatic necrosis on contrast enhanced computed tomography (CT) and the CT Severity Index (CTSI) as measured 5-7 days after admission. Peripancreatic necrosis (only) is defined as persistent peripancreatic fluid collections on a CT performed more than 14 days after admission in the absence of pancreatic parenchymal necrosis.

• Abdominal pain as daily measured by the Visual Analogue Scale (VAS).

• Proportion of daily nutritional target achieved at 1 week after admission.

• Nutrition related complications: diarrhea, aspiration pneumonia, need for conversion from EN to PN or additional PN and need for replacement of nasojejunal feeding tube after dislocation.

• Number of days until intake of solid food.

• Number of patients without the need for tube feeding in the selective delayed EN Group.

• Proportion of cross-over between both study arms.

• Hand grip muscular strength measured by the Jamar dynamometer.

• Quality of life measured by the EQ5D and SF-36 questionnaires.

• Total direct medical and indirect costs from a societal perspective during admission and until 6 months after discharge (details are available in the Additional File 1).

### Study Population

All patients admitted with a first episode of acute pancreatitis to one of the 20 participating hospitals of the Dutch Pancreatitis Study Group (DPSG, hospitals are listed below) will be assessed for eligibility within 24 hours after hospital admission. Potential eligible patients are followed during the first 24 hours after admission until eligibility is established or the first 24 hours following admission have passed. If patients are classified as 'predicted severe' acute pancreatitis, they are included and stratified for hospital and APACHE-II score <13 or ≥13 and randomised in a 1:1 ratio, to receive early EN or an oral diet or EN if necessary at 72 hours after admission (figure 1) [20].

**Figure 1 F1:**
[figure not shown]
**Flow of participants PYTHON trial according to CONSORT**.

### Inclusion criteria

• Diagnosis of acute pancreatitis if at least 2 of the 3 following features are present: 1) upper abdominal pain, 2) serum lipase or amylase levels above 3 times the upper level of normal and 3) characteristic findings of acute pancreatitis on cross-sectional abdominal imaging.

• Predicted severe pancreatitis within 24 hours after admission defined as one or more of the following (for definitions see Additional File 1; Tables S3 and S5):

- APACHE-II score ≥ 8

- Imrie-score ≥ 3

- CRP level > 150 mg/L

• Age ≥ 18 years

• Written informed consent

### Exclusion criteria

• History of acute or chronic pancreatitis

• Identification of patients > 24 hours after admission

• Onset of symptoms > 96 hours (4 days) before admission

• Acute pancreatitis due to malignancy or post-ERCP pancreatitis

• Diagnosis of acute pancreatitis confirmed during laparotomy for acute abdomen

• Artificial nutrition at admission (EN or PN)

• Pregnancy

### Treatment protocol

After the diagnosis has been established, the disease has been characterized as 'predicted severe' and written informed consent has been obtained, the patient will be randomised.

### Group A: Very early start of EN, i.e. within 24 hours

A nasojejunal feeding tube is placed either endoscopically or radiologically. If placed endoscopically, an abdominal X-ray is performed to check the tube's position and in case of radiological placement, fluoroscopy is used. Nasojejunal placement is considered correct, when the tip of the tube is placed beyond Treitz' ligament. After tube placement (figure 2), EN is started immediately using a very strict volume regimen: 20 ml/h in the first 24 hours, 45 ml/h, between 24-48 h, 65 ml/h, between 48-72 hours and, at 72 hours and thereafter: full nutrition, defined as an energy target of 25 kcal/kg/day (ICU patients) and 30 kcal/kg/day (non ICU patients) [21,22].

**Figure 2 F2:**
[figure not shown]
**PYTHON flowchart**.

### Group B: oral diet and EN if necessary at 72 hours after admission

Following randomisation, patients will be kept 'nil by mouth' without any artificial nutrition during the first 72 hours after admission (figure 2). If patients spontaneously request for oral food within these 72 hours, liquid and solid food are offered as requested and tolerated ("*ad libitum*"). If, at 72 hours after admission, patients develop organ failure, they will receive nasojejunal feeding with the same regimen as in group A. If, at 72 hours, there is no organ failure, patients are offered oral food *ad libitum*. If oral food is not tolerated, there is a re-challenge the next morning and if still not tolerated, EN is started through a nasojejunal feeding tube.

### General nutrition regimen

At 72 hours after the start of enteral feeding, the nutritional status will be evaluated and in case of intolerance, the type of EN will be changed accordingly (additional proteins, calories, fibers etc.). The patient is weighed twice a week during the first month after randomisation and once a week until discharge thereafter. If feeding is not tolerated EN is reduced to 50% and stepwise rebuilt gradually until tolerated. If, after two of such attempts, full nutrition can not be attained, PN will be started to reach the required energy target. Oral normal feeding is started, when abdominal pain has resolved and organ failure has subsided. In case of full tolerance of oral food nasojejunal feeding is gradually decreased. If pain relapses, EN is restarted. In case of nausea or vomiting, lowered consciousness (Glasgow Coma Score [GCS] 14 or lower in a non-intubated patient), or gastric residual volume (GRV) > 250 ml/6 hours, the position of the feeding tube is checked (see Additional file 1; figure S1).

### Patients in the Intensive Care Unit (ICU)

In case of ICU admission, irrespective of time from admission, the patient is fed according to the attending intensivist's preference (nasogastric or nasojejunal; enteral or parenteral). These patients are analyzed according to the treatment assigned.

### General treatment regimen

All patients will undergo contrast enhanced CT within 5-7 days after admission. Intravenous antibiotics are administered based on culture results and not as prophylaxis in case of necrotizing pancreatitis without documented infection. Invasive intervention for (suspected) infected necrosis is preferably postponed until the fluid collections are walled-off and demarcated on CT-scan. The type of antibiotics administered depends on local guidelines and is left to the discretion of the attending physician. ERCP is performed in case of suspected cholangitis or in case of biliary pancreatitis with clinically important persistent cholestasis. Patients can be discharged from hospital once abdominal pain has resolved, infection variables (leucocytes, CRP) have decreased to near normal and a normal oral diet is tolerated.

### Randomisation

Randomisation is performed centrally by the study coordinator using an internet randomisation module (Julius Center for primary care and health sciences, University Medical Center Utrecht, the Netherlands). Randomisation is stratified according to the predicted severity of disease ('predicted moderate severe' vs. 'predicted very severe'; APACHE-II < 13 or ≥ 13) and according to hospital. Permuted-block randomisation with varying block size is used and block size is concealed to all local investigators.

### Data collection and follow-up

Follow-up visits will take place at 3 and 6 months after discharge. Data collection will be performed by local physicians using a written case-record form. An independent auditor will check all primary and secondary endpoints and at least 10% of data in case-record forms against on-site source data. Discrepancies detected by the auditor will be resolved on the basis of consensus by two investigators unaware of the study-group assignment and not involved in patient care.

### Safety

An independent data and safety monitoring committee (DSMC) will evaluate the progress of the trial and will examine safety variables after every 25 patients have completed the 6 months follow-up. This evaluation is based on unblinded data, in the presence of the study coordinator as far as the 'explanatory part' of the meeting is concerned. After full explanation of the data presented, the study coordinator is dismissed and the DSMC discusses the consequences of the data presented. Adverse events are defined as 'any undesirable experience occurring to a subject during a clinical trial, whether or not considered related to the intervention' (i.e. early enteral nutrition). All involved physicians will repetitively be asked to report any potential adverse events. These adverse events will be listed and discussed with the DSMC. The outcome of the meeting of the DSMC will be discussed with the trial steering committee. The outcome will also be sent to the Utrecht institutional review board (IRB). The data of the deceased patients will be evaluated by the DSMC for cause of death and possible trial related serious adverse events. All possible adverse events will be reported to the Central Committee on Research involving Human Subjects (Centrale Commissie Mensgebonden Onderzoek [CCMO]) and the IRB using the online module https://toetsingonline.ccmo.nl 

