## Statistical Aspects

### Sample size calculation

The PYTHON trial is a superiority trial, hypothesizing a reduction in the primary endpoint in favour of early EN as compared to the current practice of an oral diet and EN, if necessary at 72 hours after admission. Data from patients in the PROPATRIA trial are used to calculate sample size [23]. All patients in the placebo-arm of the PROPATRIA trial received EN via a nasojejunal feeding tube. Patients from the PROPATRIA trial that fulfilled the PYTHON inclusion criteria (predicted severe acute pancreatitis < 24 hours after admission) were evaluated. In these patients EN was initiated after a median of 3 days. This equals the standard group in the PYTHON trial. In 39% of these patients an infection (bacteraemia, pneumonia, infected necrosis) occurred. The mortality in the placebo arm of PROPATRIA was 6%. All studies included in a meta-analysis performed by our group on EN versus PN that initiated EN within 24 hours after admission were selected [17]. In these patients (receiving EN within 24 hours), infections were diagnosed in 22% and mortality was 5%. Therefore, the expected reduction in mortality is only 1%. When mortality and infections are combined in the primary composite endpoint, an absolute reduction of 18% is expected (from 40 to 22%). With 80% power, two-sided 5% alpha and 1% loss to follow-up the sample size was set at 208 patients [http://www.stat.ubc.ca/~rollin/stats/ssize/b2.html].

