### Premature termination of the study

An interim-analysis is performed on the primary endpoint when 50% of patients have been randomised and have completed the 6 months follow-up. The interim-analysis is performed by an independent statistician, blinded for the treatment allocation. The statistician will report to the independent DSMC. The DSMC will have unblinded access to all data and will discuss the results of the interim-analysis with the steering committee in a joint meeting. The steering committee decides on the continuation of the trial and will report to the central ethics committee. The Peto approach is used: the trial will be ended using symmetric stopping boundaries at P < 0.001 [25]. The trial will not be stopped in case of futility, unless the DSMC during the course of safety monitoring advices otherwise. In this case DSMC will discuss potential stopping for futility with the trial steering committee.

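### DSMC safety reviews are triggered by completed 6-month follow-up, so the first by-arm review comes with about 60 of 208 patients already randomised

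*Protocol article*

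**What the plan says.** In the protocol article, the Safety section gives the DSMC's timetable: it "will examine safety variables after every 25 patients have completed the 6 months follow-up". The evaluation uses unblinded data. The same section says that physicians are asked repeatedly for adverse events, that these are listed and discussed with the DSMC, that the DSMC evaluates deaths for cause and relation to the trial, and that events go to the CCMO and the IRB. None of these channels is given a date or a patient count of its own.

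The planned pace is in the abstract: "During a 3-year period, 208 patients will be enrolled from 20 hospitals". The primary endpoint counts events "occurring during hospital admission or within 6 months following randomisation". Data collection and follow-up sets its visits on a later clock: "Follow-up visits will take place at 3 and 6 months after discharge".

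Premature termination of the study adds one interim analysis of the primary endpoint, when half the patients have been randomised and followed for 6 months. There "the trial will be ended using symmetric stopping boundaries at P < 0.001".

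**The concern.** The arms differ in feeding during the first 72 hours after admission (Group A and Group B sections). Several of the protocol's own harm-relevant measures become known early: first-week APACHE-II, SIRS and CRP, nutrition-related complications such as aspiration pneumonia, and in-hospital mortality. A trigger that waits for 25 patients to finish 6 months adds little to that early information, but it postpones the first occasion on which anyone independent compares the arms. Meanwhile recruitment goes on. At the other end of the trial, reviews that fall after the last patient has entered cannot change how any patient is allocated.

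**Working it through.** **Inputs.** 208 patients, 36 months and a review per 25 completers (abstract; Safety). Follow-up is 6 months from randomisation (Primary endpoint). Even accrual is my assumption.

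**The plan's own figure.** The sample size section states: "With 80% power, two-sided 5% alpha and 1% loss to follow-up the sample size was set at 208 patients". With event rates of 40% and 22% and mean 0.31:

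n per arm = [1.96·√(2·0.31·0.69) + 0.842·√(0.40·0.60 + 0.22·0.78)]² / 0.18² = (1.282 + 0.540)² / 0.0324 ≈ 102.5, rounded up to 103.

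The total is 206, and 206/0.99 = 208.1. The stated 208 is reproduced, so it is a sound basis for the accrual rate.

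**Accrual.** 208/36 = 5.78 per month. In 6 months, 6 × 5.78 = 34.7 patients enter.

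**Timing under the plan.** The review at k completers falls at month k/5.78 + 6, with min(208, k + 34.7) randomised. If the trigger were k patients randomised, it would fall at month k/5.78.

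| k | Month, as planned | Randomised by then | Month, if triggered by k randomised |
|---|---|---|---|
| 25 | 10.3 | 60 | 4.3 |
| 50 | 14.7 | 85 | 8.7 |
| 75 | 19.0 | 110 | 13.0 |
| 100 | 23.3 | 135 | 17.3 |
| 125 | 27.6 | 160 | 21.6 |
| 150 | 32.0 | 185 | 26.0 |
| 175 | 36.3 | 208 (closed at 36.0) | 30.3 |
| 200 | 40.6 | 208 (closed) | 34.6 |

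At the first review 59.7/208 = 29% of the trial is randomised. The efficacy interim (104 completers) comes at month 24.0 with about 139 randomised, so it is no earlier safeguard.

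**Sensitivity.**
- A start-up ramp of 3 or 6 months, still reaching 208 at month 36: 61 to 63 randomised at the first review, and the last two reviews still after closure.
- Follow-up counted from discharge, with an assumed stay of 0.5 to 1 month: 63 to 65 at the first review, and the 175 review at month 36.8 to 37.3.
- Faster accrual, 7 per month: 67 at the first review.
- Slower accrual: Recruiting success reports 142 randomised without dating the count. If it were the publication date, 30.7 months after the first randomisation, the rate would be 142/30.7 = 4.62 per month. The first review would then have about 53 randomised, and the 175 review (month 43.9) would precede closure (month 45.0). That section also says recruitment is faster than planned, which instead implies at least 5.78 per month.
- Break-even: the 175 review follows closure only if 175 + 6r > 208, that is, r > 33/6 = 5.5 per month. The 200 review follows closure for any r > 8/6 = 1.3 per month.

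The first-review figure therefore ranges from about 53 to 67. The 200 review is late in every scenario. The 175 review depends on the rate.

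**The case against.** The strongest reply is that the trigger fixes when the DSMC meets, not which patients it sees. The Safety section does not restrict the unblinded data to completers, and adverse events and deaths reach the DSMC without that restriction. After the first review the meetings recur every 25/5.78 = 4.3 months. This stands. A reader might infer that every harm signal is seen half a year late throughout the trial; the text does not show that. What remains is the late first review and the thin cover near the end.

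Second, eight unblinded reviews in 208 patients is frequent oversight, and 6 months matches the primary endpoint window, so completed patients give comparable counts. That is a fair reason for the choice, but it serves the efficacy endpoint better than early safety.

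Third, a review at 25 patients is statistically weak. With 12 or 13 per arm and the 6% mortality quoted in the sample size section, about 0.06 × 12.5 = 0.75 deaths per arm are expected. Such a review supports clinical judgement, not a test. This also stands.

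A reader might further infer that the P < 0.001 boundary leaves excess mortality unguarded and that a mortality threshold is needed. The documents do not support this. The boundary applies to the composite at one interim; it is not a mortality rule. The DSMC is left free to weigh the safety data without a numerical threshold, and any advisory guideline belongs in its charter, which is not shown.

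**Conclusion.** The point holds as a low-cost improvement to the timing of safety reviews; it is not a contradiction in the plan. At the planned rate with even accrual, the first by-arm review comes at about month 10 with about 60 of 208 patients randomised (53 to 67 across the scenarios tried), and the review at 200 completers comes after enrolment has closed. It would be too strong to say that the last two reviews are both clearly too late: the 175 review misses closure by 0.3 month and would precede it below 5.5 patients per month. It would also be too strong to say that patients are unprotected in the meantime, because adverse events and deaths reach the DSMC and events go to the CCMO and the IRB. What is missing is any stated earlier trigger for comparing the arms.

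**What to change.** Reword the Safety section so that the DSMC reviews safety after every 25 patients randomised. Each review should present all data available to date by arm: deaths, organ failure, infections and nutrition-related complications. It should not wait for 6-month completion. Leave the efficacy interim and its boundary as they are.

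At the planned rate the number of reviews stays at eight (208/25 = 8.3). Each comes 6 months earlier, the first at about month 4.3 and the last at about month 34.6, before closure at month 36.

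The cost is a change of wording. Recently randomised patients would contribute incomplete and not yet audited follow-up, so each report should show length of follow-up by arm. Because the article reports 142 patients already randomised, the earlier first review can no longer be gained here. The change would still bring the remaining reviews forward while the last 208 − 142 = 66 patients are entering.
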